## Abstract

**Background:** Joint contractures are common problems in frail older people in nursing homes. Irrespective of the exact extent of older individuals in geriatric care settings living with joint contractures, they appear to be a relevant problem. Also, the new emphasis on the syndrome of joint contractures, e. g. by the German statutory long term care insurance, led to an increase in assessment and documentation efforts and preventive interventions in clinical care. However, more attention should be paid to the actual situation of older individuals in nursing homes with prevalent joint contractures, particularly their experience of related activity limitations and participation restrictions. Thus, the aim of this study is 1) to develop a tailored intervention to improve functioning, and especially participation and quality of life in older residents with joint contractures in nursing homes and 2) to test the feasibility of the intervention accompanied by a rigorous process evaluation.

**Methods:** The complex intervention, which will be developed in this project follows the UK Medical Research Council (MRC) framework and integrates the perspectives of all potentially relevant user groups, from the affected individuals to clinicians and researchers. The development process will comprise a systematic literature review, reanalysis of existing data and the integration of the knowledge of the affected individuals and experts. The developed intervention including a comprehensive process evaluation will be pilot tested with residents with joint contractures in three nursing homes.

**Discussion:** The projected study will provide a tailored intervention to improve functioning, participation and quality of life in older residents with joint contractures in nursing homes. With this focus, the intervention will support patient relevant outcomes. The pilot study including process evaluation will offer a first opportunity to indicate the size of the intervention’s effect and prepare further studies.

## Background

Joint contractures are associated with restrictions in full range of motion of any joint due to deformity, disuse, and pain. They are common problems of frail older people, particularly in nursing home residents [1], [2]. Irrespective of the various causes and underlying health conditions, e.g. neurological or musculoskeletal conditions, joint contractures can have significant impact on overall quality of life and functioning of the affected individuals, limit daily activities and mobility and lead to other negative consequences, such as pain or increased risk of falls [3], [4], [5], [6], [7]. 

Prevalence data on joint contractures are scarce and estimates vary widely, presumably due to different definitions and populations. Studies involving nursing home residents in the US report prevalence rates between 25% [8] and 80% [2], [3], [6], [9], [10]. 

Irrespective of the exact number of older individuals in geriatric care settings living with joint contractures, joint contractures appear to be a relevant problem and receive growing attention. For example, the German federal statutory long term care insurance system has defined the assessment of risk for joint contractures and the implementation of preventive measures as quality indicators in long-term nursing care [11], [12], [13]. This new emphasis on the syndrome of joint contractures led to an increase in assessment and documentation efforts and preventive interventions in clinical care [14], even though evidence for the effectiveness of preventive measures is lacking [15], [16], [17]. 

As proofs of effectiveness are missing for the primary and secondary preventive interventions that are part of the current standard of care in joint contractures, an alternative focus should be on interventions which do not merely address prevention or treatment of joint contractures but also focus on maintaining or enhancing participation and quality of life. Thus, more attention should be paid to the actual situation of older individuals in nursing homes with prevalent joint contractures, particularly their experience of related activity limitations and participation restrictions. To address this issue, we have recently developed a standard set based on the WHO’s International Classification of Functioning, Disability and Health (ICF) [18] to comprehensively describe activity limitations and participation restrictions and are developing a standardized assessment instrument to quantify the extent of activity limitations and participation restrictions [19]. Based on the results of the preceding project the next step is now to develop an intervention to address the actual situation of older individuals in nursing homes with prevalent joint contractures. Hence, the aim of this study is 1) to develop a tailored complex intervention to improve functioning, and especially participation and quality of life in older residents with joint contractures in nursing homes and 2) to test the feasibility of the intervention and the process evaluation tools in a pilot study. 

## Methods

The development of relevant, effective and feasible health care interventions is challenging, since changes in health care practice are rather complex than deterministic. To address these issues und to ensure the development of theoretically and empirically plausible, consumer-orientated and feasible interventions, the UK MRC framework was introduced to provide guidance on how to develop and evaluate complex interventions. It identifies the following four key elements of this potentially cyclical process: development, feasibility/piloting, implementation and evaluation. This study protocol focuses on the development and the feasibility/piloting phases. The development phase usually includes identification of the relevant evidence base, identification or development of a theory and modelling of the intervention process and the addressed outcomes. In the feasibility and piloting stage, the acceptability and feasibility of the developed intervention is carefully assessed. Also, recruitment procedures and recruitment and retention rates have to be evaluated. In addition, the basis for sample size calculations can be investigated in this phase [20], [21]. Based on this framework, our study has a design with seven successive steps. 

An overview of all applied methods and designs is given in Table 1 (Tab. 1). 

The study protocols of all empirical parts of the projects will be presented to the respective ethics committees of the Ludwig-Maximilians-Universität in Munich and the Martin-Luther-University in Halle-Wittenberg prior to the start of the respective part. Written informed consent from the participants or their legal guardians will be obtained prior to inclusion in the study.

### (1) Identification of evidence (development phase): Systematic Review

**Aims: **The aim of this systematic review is to identify the existing evidence regarding prevention and/or treatment of disability due to joint contractures which serves as basis for the intervention modelling. 

**Methods: **The systematic review will be carried out in electronic databases (PUBMED, CINAHL, EMBASE, Psychinfo) and via hand searches. The process and results will be documented using an electronic database. The review will include randomized and non-randomized controlled trials on programs for prevention and/or treatment of disability due to acquired joint contractures. Target population are individuals in need for long term care of either type. 

**Analysis:** The critical appraisal will follow the Cochrane Handbook for Systematic Reviews of Interventions, version 5.1.0 [22]. Since retrieved studies are expected to be too diverse to be analysed by means of a meta-analysis, a narrative synthesis as suggested by the York University Centre for Reviews and Dissemination ([23], p. 48) will be carried out. A detailed description of the review protocol can be found at PROSPERO (http://tinyurl.com/JCISystRev).

### (2) Identification of intervention goals (development phase): Graphical model

**Aims: **The aim of the graphical models is to identify ICF categories which could serve as intervention targets. Graphical models depict association structures between variables with complex interactions and differentiate confounding variables from intermediate variables [24], [25], [26]. Graphical models lead to network-like graphs in which hubs, i.e. nodes with several connections to other nodes, can be identified. By addressing such hubs by targeted interventions, many other categories may be influenced. 

**Participants and design: **We will apply graphical modelling to existing data on prevalence of functioning and disability in patients with joint contractures [7], [27]. In brief, the study sample to be analysed consists of a cross-sectional sample of 299 older patients (>65 years) with joint contractures in geriatric care settings (acute and post-acute specialized rehabilitation, nursing home). Functioning and disability was appraised by 124 categories of the International Classification of Functioning, Disability and Health. Among those, 28 categories referred to the ICF component body functions, 80 to activities and participation and 16 to environmental factors. Data will be dichotomized in “no problem” vs. “any problem”.

**Analysis:** Since graphical models are susceptible to small changes in the data set leading to great changes in the result, we implement bootstrap aggregating (bagging) to stabilize the outcome of such a model and subsequently enhance accuracy [28], [29], [30] and validity of the results. Multiple imputations will be used to adequately handle missing values in our data set [31]. To develop a graphical model, the conditional independencies will be identified via the neighbourhood of a variable. The neighbourhood of a variable is defined as the set of conditionally dependent variables. Meinshausen and Buehlmann [32] showed that neighbourhood selection by means of the so-called least absolute shrinkage and selection operator (LASSO) [33] is superior to common methods, in particular, if the number of variables exceeds the number of observations. The set of predictor variables corresponding to nonzero coefficients in a prediction model represents the neighbourhood. By estimating the neighbourhood for each variable the whole graphical model can be identified. 

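### The planned graphical model is undirected and cannot tell confounders from intermediates; with care settings pooled, some hubs may also reflect setting

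*Protocol article*

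**What the plan says.** All of the following is in the protocol article, section (2), Graphical model.

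- **Claimed property.** Under Aims, graphical models are said to "differentiate confounding variables from intermediate variables".
- **Use of the result.** Hubs are the candidate targets: "By addressing such hubs by targeted interventions, many other categories may be influenced".
- **Data.** A "cross-sectional sample of 299 older patients (>65 years) with joint contractures in geriatric care settings (acute and post-acute specialized rehabilitation, nursing home").
- **Variables.** "Functioning and disability was appraised by 124 categories of the International Classification of Functioning, Disability and Health", of which "28 categories referred to the ICF component body functions, 80 to activities and participation and 16 to environmental factors". Each is dichotomised as no problem or any problem. Care setting is not mentioned as a node, covariate or stratum.
- **Estimator.** LASSO neighbourhood selection with bagging and multiple imputation. "The neighbourhood of a variable is defined as the set of conditionally dependent variables", and "By estimating the neighbourhood for each variable the whole graphical model can be identified".

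The Abstract, Background and section (6) restrict the intervention and its pilot to nursing home residents. Sections (3) to (5) add focus groups with residents, an expert panel and a Delphi survey before the components are settled.

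**The concern.** There are two separate problems.

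**Direction.** Separating a confounder from an intermediate needs information on direction: time order, an imposed ordering of variables, or an intervention. The section describes none of these. Its estimator returns only which variables are conditionally dependent. The stated reason for choosing hubs is nevertheless causal in tone, since it says that acting on a hub may influence many other categories. A category that is a downstream marker of many problems also has many connections, and changing it need not change anything else.

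**Setting.** Suppose many categories are problems more often in one setting than in another. They then become associated in the pooled data even if they are unrelated within each setting. Bagging addresses sampling instability. It does not remove an association that is present in the pooled population and so tends to recur in the bootstrap samples.

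At stake is which categories reach the expert panel as promising targets for nursing home residents.

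**Working it through.** **1. The plan's own figure.** 28 + 80 + 16 = 124 categories, which reproduces. The number of possible pairs is 124 × 123 / 2 = 7,626. The step states no sample-size, power or alpha figure to check.

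**2. Confounder and intermediate give the same distribution.** The probabilities here are illustrative.
- Fork (Z is a common cause of X and Y): P(Z=1) = 0.5; P(X=1|Z) = 0.7 for Z=1 and 0.3 for Z=0; P(Y=1|Z) = 0.6 for Z=1 and 0.2 for Z=0.
- Chain (X acts on Y through Z): the fork implies P(X=1) = 0.5 × 0.7 + 0.5 × 0.3 = 0.5 and P(Z=1|X=1) = 0.35/0.5 = 0.7. Keep P(Y|Z) as it is.
- Example cell, X=Z=Y=1: fork 0.5 × 0.7 × 0.6 = 0.21; chain 0.5 × 0.7 × 0.6 = 0.21. Over all eight cells the largest difference is 0.0.

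In both cases X and Y are independent given Z, so both give the graph X–Z–Y. No sample size and no amount of bagging can separate them.

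**3. What pooling does to one pair.** Assumption: two settings of equal size, and two categories that are independent within setting with prevalence 50% and 90%.
- P11 = (0.25 + 0.81)/2 = 0.53; P10 = P01 = (0.25 + 0.09)/2 = 0.17; P00 = (0.25 + 0.01)/2 = 0.13.
- Odds ratio = 0.53 × 0.13 / 0.17² = 2.38.
- phi = (0.53 − 0.70²)/(0.70 × 0.30) = 0.04/0.21 = 0.19; z = √299 × 0.19 = 3.3.
- With 60% and 90% the odds ratio is 0.585 × 0.085 / 0.165² = 1.8.

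**4. Why those figures overstate the signal.** They are marginal, whereas the model estimates dependence given the other items. If k items share the same pairwise correlation ρ, the partial correlation of a pair is ρ/(1 + (k − 2)ρ).
- k = 10: 0.19/(1 + 8 × 0.19) = 0.075; z ≈ √299 × 0.075 = 1.3.
- k = 30: 0.19/(1 + 28 × 0.19) = 0.03; z ≈ √299 × 0.03 = 0.5.

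Penalised selection can still admit false edges, because the penalty keeps it from adjusting fully for the other items. Simulation is therefore needed.

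**5. Simulation.** n = 299 and 124 binary items with no links within setting; linear LASSO neighbourhoods, with an edge kept only if both regressions select it; 20 runs per scenario; no bagging or imputation. Assumptions: one setting holds 1/3 or 1/2 of patients, 10 or 30 items differ by setting, and prevalence is 50% plus or minus half the gap. Penalty A is the Meinshausen-Bühlmann type at alpha 0.05. Penalty B is a looser λ = 0.13. Each range covers the two setting splits.

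| Items differing | Prevalence gap | A: false edges, pooled | A: largest degree, pooled | A: false edges, setting adjusted | B: largest degree, pooled | B: largest degree, setting adjusted |
|---|---|---|---|---|---|---|
| 30 | 0 | 0 | 0 | 0 | 7.0–8.2 | 7.2–8.0 |
| 30 | 0.2 | 0 | 0 | 0 | 7.7–8.2 | 7.5–7.6 |
| 30 | 0.4 | 4.2–7.4 | 1.8–2.4 | 0 | 14.4–15.1 | 7.4–7.6 |
| 30 | 0.6 | 80.6–86.4 | 10.2–11.0 | 0 | 17.6–18.5 | 7.1–7.4 |
| 10 | 0.4 | 0.5–1.4 | 0.4–1.0 | 0 | 8.6–9.1 | 7.2–7.3 |
| 10 | 0.6 | 18.0–19.8 | 6.0–6.3 | 0 | 9.8–9.9 | 7.2 |

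With no setting difference, penalty B already produces about 163 to 172 chance edges, so its degrees must be read against a background of 7 to 8. False hubs need a large gap across many items, and how large depends on the penalty. Adjusting for setting returns every scenario to its background level.

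**The case against.** - **The sentence on confounders is a general, cited statement about a class of models.** The section also speaks of association structures, and says only that categories could serve as targets. This is fair: no causal effect is to be estimated, and some graphical models with an imposed ordering may have the property. The model described here does not, and the sentence is offered in support of it. The correction stands, whatever a fuller protocol says about setting.
- **Silence about setting in a condensed article is not proof of omission.** This stands. The article describes its data only in brief, and the full protocol may adjust or stratify. The environmental-factor categories may also act as a partial proxy for setting. The setting point is therefore a check to make and not a demonstrated error.
- **A reader might infer that the hubs are artefacts of setting, citing the odds ratio of 2.4 and z of 3.3.** The documents do not support that. Those figures are marginal, the matching conditional signal is small, and neither the prevalence gaps nor the setting split is given.
- **Conditioning on setting is itself debatable.** Poor functioning may lead to nursing-home admission, so setting may be partly a consequence of the categories, and adjusting for it could induce associations. Dropping every hub that fails to persist in a smaller subsample would partly select on power. Both points stand, and they argue for a sensitivity analysis and not a new primary rule.
- **Hubs are one input among several.** Focus groups, expert panel and Delphi survey also shape the components. This stands and lowers the priority. Still, nothing described would alert the panel that a hub carries no direction or may reflect setting.

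**Conclusion.** The claim that the model separates confounding from intermediate variables is wrong for the model planned here. This follows from the stated design and estimator and needs no assumption about the data. A hub from this analysis shows association only.

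The pooling point holds conditionally. Setting-driven edges and hubs are possible if prevalence differs strongly by setting across many categories. Under the stricter penalty with 30 such items, the simulation gave no false edges at a gap of 0.2, about 4 to 7 at 0.4, and about 81 to 86 (largest degree 10 to 11) at 0.6. These results rest on assumed splits, gaps and penalties and leave out the planned bagging, so they show a range and not an estimate for this trial.

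Priority is low to moderate. The issue concerns the choice of intervention targets in the development phase and does not affect the pilot trial's analysis.

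**What to change.** 1. In section (2), remove the confounder/intermediate claim or correct it for this model, and state that the graph is undirected.
2. Present the hubs to the expert panel as undirected associations, to be weighed with the focus-group goals and the other inputs already planned.
3. As a sensitivity analysis, re-run the model with care setting as a node or an unpenalised covariate, and again in the nursing-home subsample. Report the number of patients per setting and tell the panel which hubs change. Do not use persistence as a hard exclusion rule.

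The cost is a wording change and two further runs on existing data. Edges in the nursing-home subsample will be less stable because it is smaller, and the report to the panel should say so. If the full protocol already handles setting, only items 1 and 2 remain.

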### (3) Identification of intervention goals (development phase): Focus groups

**Aims:** To also incorporate the consumer perspective, focus group interviews with nursing home residents affected by joint contractures will be carried out as a complimentary approach to the data driven identification of potential intervention goals by graphical models. In the focus groups, desirable goals and potential facilitators and barriers to reach these goals will be discussed [34]. 

**Participants and design:** The focus groups with residents will take place in the cooperating nursing homes. To ensure adequate communication, a maximum of five participants are feasible since they will be of old age and presumably frail. Therefore, four focus groups resulting in a sample size of approximately 20 participants will be planed. Final sample size will be determined by saturation. Saturation refers to the point at which an investigator has obtained sufficient information from the field [35]. The focus groups with affected individuals [34] will follow quantitative descriptive methodology [36]. A possible source of bias for the focus groups is the recruitment of participants, which have to be able to participate and to communicate adequately. This selection could introduce bias towards individuals with milder disease and less severe problems. Even with the risk of bias in mind, focus groups are able to result in more comprehensive data than individual interviews [37]. This is especially true for those individuals planned to be included in our study who share the same living environment and associated barriers and facilitators because they might put each other in mind of relevant aspects. In addition, experiences from prior individual interview studies with nursing home residents with joint contractures indicate feasibility [38]. 

**Analysis:** The results of the focus groups will be categorized using content analysis according to the concept of qualitative description [36], [39] by two independent researchers. 

### (4) Identification and development of intervention components (development phase): Expert panel

**Aims:** To develop a preliminary list of intervention components, a structured two-day meeting with renowned national clinical experts will be held. 

**Participants and design:** The results of the systematic review, the potential intervention goals and the focus groups as well as the results of the qualitative interviews from our previous project [38] will be presented. The results of the qualitative interviews will be introduced at this point to further address the patients’ perspective. The expert consultation will be organized as a formal consensus building process where a group of experts will engage in plenary discussion and smaller working groups. All steps of the consensus process will be documented in an electronic database. The expert panel will be constituted by inviting outstanding national experts in the field of geriatric care and medicine and will comprise about 10 persons. 

### (5) Identification and development of intervention components (development phase): Expert Delphi survey

**Aims:** The results from step 4 will be further validated in an expert Delphi survey. 

**Participants and design:** The potential intervention components will be evaluated and missing aspects can be mentioned in up to three rounds [40]. The survey will be carried out via an online platform and will involve health professionals from all relevant professions (nurses, physicians, physical therapists, occupational therapist) and all relevant fields (nursing homes, geriatric rehabilitation, acute care hospitals). Inclusion criteria will be clinical expertise (work experience >5 years in geriatric care settings, i.e. hospitals, rehabilitation facilities and nursing homes). The experts will be selected from an existing data base from the previous project where they have committed for participation. Further sources of contacts are both suggestions from other experts and professional organizations and identification through authorship of relevant publications. Literature on Delphi surveys suggests a group size of about 20 [41]. We will carry out a separate survey for physicians, nurses and therapists. 

**Analysis: **The results of the Delphi survey will be categorized using content analysis according to the concept of qualitative description [36], [39] by two independent researchers. 

